# Study protocol for a prospective observational study to investigate the role of luminal pressure on arteriovenous fistula maturation

**DOI:** 10.1097/MD.0000000000017238

**Published:** 2019-10-04

**Keywords:** arteriovenous fistula (AVF), end-stage renal disease, hemodialysis, luminal pressure, vascular access

## Abstract

**Introduction::**

Arteriovenous fistula (AVF) is the preferred vascular access for hemodialysis due to its higher patency and lower infection rate. However, its suboptimal maturation rate is a major weakness. Although substantial risk factors for AVF maturation failure have been disclosed, modifiable risk factors remain unknown. During the AVF maturation process, an elevated luminal pressure is required for outward remodeling; however, excessively high luminal pressure may also be detrimental to AVF maturation, which remains to be defined. We hypothesized that higher AVF luminal pressure is harmful to its maturation, and investigate its potential as a modifiable factor to improve AVF maturation.

**Methods and analysis::**

This prospective study includes patients undergoing surgical creation for a native AVF. The exclusion criteria were as follows: age <20 years, inability to sign an informed consent, and failure to create a native AVF due to technical difficulties. Demographic and laboratory profiles will be collected before AVF surgery. Vascular sonography will be performed within 1 week of AVF creation to measure the diameters, flow rates, and flow volumes of AVF and its branched veins. The pressure gradient within AVF will be estimated from the blood flow rates using the modified Bernoulli equation. The primary outcome is spontaneous AVF maturation defined as provision of sufficient blood flow for hemodialysis within 2 months of its creation without any interventional procedures. The secondary outcome is assisted AVF maturation, which is defined as AVF maturation within 2 months from its creation aided by any interventional procedure before the successful use of AVF.

**Discussion::**

While contemporary theory for AVF maturation failure focuses on disturbed wall shear stress, complicate assumptions and measurement preclude its clinical applicability. AVF luminal pressure, which may be manipulated pharmaceutically and surgically, may be a target to improve the outcome of AVF maturation.

**Trial registration::**

This study has been registered at the protocol registration and results system. The Protocol ID: NCT04017806.

## Introduction

1

In Taiwan, the burden of end-stage renal disease has been increasing tremendously over the last two decades. According to the 2017 Annual Report on Kidney Disease in Taiwan, the prevalence of patients requiring dialysis has increased from 1379 per million population in 2000 to 3317 per million population in 2015, thereby demonstrating an increasing rate of 11.1% per year.^[1]^ In patients on dialysis treatment, vascular access dysfunction is the most common cause of medical procedures, including angioplasty, thrombectomy, and placement of central venous catheters, thereby indicating a need for improved medical care associated with vascular access.^[2]^

Arteriovenous fistula (AVF) was introduced as a vascular access for hemodialysis by Brescia et al^[3]^ and remains the most commonly used vascular access to date.^[4]^ Due to its superior access patency and lower infection rates, AVF is the preferred vascular access for maintenance hemodialysis.^[5]^ However, AVF is not an ideal vascular access without drawbacks. One of its major flaws is that only 50% to 80% of the created AVFs achieve functional maturation for hemodialysis,^[6–8]^ which results in infectious and thromboembolic complications due to the prolonged use of the central venous catheter.

Previous studies have revealed several risk factors of AVF maturation failure, including anemia, advanced age, diabetes mellitus, and smoking.^[9,10]^ While these risk factors may be targeted to improve AVF maturation rate, modifiable risk factors for prevention are currently lacking.^[9]^ On the other hand, basic studies have revealed molecular pathogenic factors of AVF maturation failure, including localized inflammation, hypoxic injury, oscillating wall shear stress, uremic milieu, and oxidative stress.^[11]^ Despite these substantial studies exploring the role of pathogenic factors, modifiable pathogenic factors that are applicable for improvements in AVF maturation are lacking.^[12]^

Maturation failure of AVF results from luminal stenosis due to neointimal hyperplasia, signifying a thickening of the subintimal area caused by proliferation of myofibroblasts as shown by remarkable staining for α-smooth muscle actin and vimentin.^[13]^ Neointimal hyperplasia of AVF occurs mainly at the arteriovenous junction and venous limb of AVF, where the venous endothelium is exposed to a non-physiological high blood flow rate, oscillatory shear stress, and pulsatile stretching strain by arterial blood flow, suggesting the role of altered hemodynamics on AVF subintimal proliferation.^[14]^

Physically, the human arterial and venous hemodynamics are substantially different. In the arterial system, the blood flow is pulsatile with a mean arterial pressure of 65 to 70 mmHg, while in venous system, the blood flow is non-pulsatile with a blood pressure of 5 to 10 mmHg.^[15]^ Furthermore, endothelial cells from the arterial and venous parts of the circulation system have different genetic expression profiles, indicating that different hemodynamic environments regulate phenotypes of endothelial cells.^[16]^ Therefore, it is reasonable that elevated luminal pressure may stimulate proliferation in the venous endothelium of AVF and result in maturation failure. In contrast, elevated AVF luminal pressure also provides a stretching force for outward remodeling, which is required for AVF maturation. As such, an optimal range of luminal pressure needs to be defined.

Consequently, we hypothesized that while elevated AVF luminal pressure is required for AVF maturation, excessive AVF luminal pressure may cause a detrimental stretching force and result in AVF maturation failure. However, an optimal luminal pressure range remains to be defined.

## Methods and analysis

2

### Main aims

2.1

The aim of this study will be conducted to investigate the optimal AVF luminal pressure for AVF maturation, which may be modified surgically or pharmaceutically to improve the AVF maturation rate.

#### Specific aims

2.1.1

**Aim 1: To characterize the altered blood flow rates and luminal pressures in different segments of AVF**

While excessive AVF luminal pressure may stimulate the proliferation of AVF venous subintima to cause maturation failure, comprehensive AVF hemodynamic profiles in different AVF segments should be characterized first. In this study, the blood flow rates will be measured at the artery-to-vein anastomosis, the bifurcation sites of AVF, and its branches after bifurcation. With these flow rate values, the pressure gradient across the AVF will be calculated. We will also estimate the absolute AVF luminal pressure using the difference between the mean arterial pressure and AVF pressure gradient. These results will provide a comprehensive hemodynamic profile of AVF and may reveal novel and valuable risk factors of AVF maturation failure.

**Aim 2: To characterize the association between luminal pressures and the vessel diameters of different segments of AVF**

Previous studies have shown that a cephalic venous diameter <2.5 mm independently predicted AVF maturation failure.^[17]^ However, the association between the vessel diameters and AVF hemodynamics is complex, and the concept that a larger vessel diameter provides higher maturation rate may be inappropriate. For example, a cephalic vein with a larger diameter may also have larger branches to offset the AVF luminal pressure and outward remodeling required for AVF maturation. In this part of the study, the association between the vessel diameters of different segments and AVF luminal pressure will be analyzed. The results will provide preliminarily evidence to support the role of vessel diameter in AVF maturation.

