#### Laboratory analysis

2.4.2

The laboratory data of pre-surgical evaluation, including hemoglobin and white blood cell count as well as levels of serum urea, creatinine, sodium, potassium, calcium, phosphorus, albumin, and parathyroid hormone will be included as covariates. Before the creation of AVF, pre-procedural vascular sonography of both arms will be performed to determine the optimal site for the AVF. After the creation of the AVF, vascular sonography of the ipsilateral arm will be repeated within 1 week to measure the diameters, blood flow rates, and blood flow volume of the AVF and its main branches as described previously. The AVF luminal pressure will be calculated from blood flow rates using the modified Bernoulli equation as described in the following section.

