#### Estimation of luminal pressure of AVF

2.4.3

For the radiocephalic AVF, the blood flow rates will be measured at the radial artery-to-cephalic vein anastomosis and the site of cephalic vein bifurcation into the basilic and cephalic veins. The luminal pressure in the radiocephalic AVF will be estimated by the pressure gradient from these two points. For the brachiobasilic AVF, blood flow rates will be measured at the brachial artery-to-basilic vein anastomosis and basilic vein-to-brachial vein junction. The luminal pressure of the brachiobasilic AVF will be estimated by the pressure gradient between these two points. For the brachiocephalic AVF, the blood flow rates will be measured at the brachial artery-to-median basilic vein anastomsosis and cephalic vein-to-subclavian vein junction. The luminal pressure of the brachiocephalic AVF will be estimated by a pressure gradient between these two points.

The blood flow rates of the AVF and its branches will be measured by Doppler ultrasound (Zonare Ultrasound System, Shenzhen Mindray Bio-Medical Electronics Co.). All Doppler ultrasound examinations will be performed by 2 rotating technicians to ensure consistency between measurements. Then, the pressure gradient between the arterial and venous ends of the AVF will be estimated using the modified Bernoulli equation as following: 

Where ΔP refers to the pressure gradient, V_1_ refers to the proximal blood flow rate, and V_2_ refers to the distal blood flow rate. The absolute blood pressure of the arterial limb of the AVF will be approximated as the mean arterial pressure of the contralateral arm. Then, the blood pressure of the AVF will be approximated with the following equation: 

Where MAP refers to the mean arterial pressure measured in the contralateral brachial artery.

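### Aim 2 claims support for a role of vessel diameter in maturation from an analysis that contains no maturation data

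*Protocol article*

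**What the plan says.** Aim 2 (section 2.1.1) plans one analysis: "the association between the vessel diameters of different segments and AVF luminal pressure will be analyzed". It introduces this by doubting a common belief, namely that "the concept that a larger vessel diameter provides higher maturation rate may be inappropriate", and gives as an example a large cephalic vein whose large branches reduce luminal pressure and remodelling. It ends with the inference "The results will provide preliminarily evidence to support the role of vessel diameter in AVF maturation".

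Pressure is not measured. Section 2.4.2 states: "The AVF luminal pressure will be calculated from blood flow rates using the modified Bernoulli equation". In section 2.4.3 the inputs to the gradient are two Doppler readings, where V1 "refers to the proximal blood flow rate, and V_2_ refers to the distal blood flow rate". Aim 1 adds that the investigators will "estimate the absolute AVF luminal pressure using the difference between the mean arterial pressure and AVF pressure gradient". Diameters and Doppler readings come from one examination: "vascular sonography of the ipsilateral arm will be repeated within 1 week to measure the diameters, blood flow rates, and blood flow volume".

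Maturation enters in Aim 3, against pressure. The logistic regression in section 2.6 does not name its predictors.

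**The concern.** The inference concerns a variable that the analysis does not contain. An author following Aim 2 as written would find that diameter correlates with calculated pressure and report this as support for a role of diameter in maturation. The same correlation would be found whether wider veins matured better, worse or no differently. Aim 2 itself doubts that wider is better, so a reader would want that doubt tested on the outcome, and Aim 2 does not do so.

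In addition, some diameter-pressure association is to be expected from the way velocity relates to flow and vessel area. Significance there says less about biology than it appears to.

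**Working it through.** **1. The plan's own figure.** Section 2.6 gives an effect size of 0.6, alpha 0.05 two-sided, power 0.8 and 1:1 allocation. The exact noncentral t calculation gives 45 per group, 90 in total, with power 0.804. The stated 90 reproduces. The protocol gives no figure for Aim 2.

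**2. Inputs against conclusion.**
- Aim 2 inputs: segment diameters and calculated pressure.
- Aim 2 conclusion: diameter and maturation.
- Aim 3 inputs: pressure and maturation.

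No aim states an analysis of diameter against maturation. If every patient's maturation status were changed and nothing else, the Aim 2 result would be identical. This step needs no assumption.

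**3. Can Aims 2 and 3 be chained?** The Introduction holds that raised pressure is needed for maturation, that excess pressure causes failure, and that an optimal range has yet to be found. Suppose a wider segment goes with higher pressure. Below the optimum that would favour maturation; above it, the reverse. The sign of the diameter-pressure association therefore does not fix the sign of any diameter-maturation association. Diameter may also act by routes other than calculated pressure, such as the wall shear stress described in the Discussion.

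**4. How far is the association mechanical?** The equation is not shown in the text at hand. I assume the usual form, gradient = 4(V1² − V2²), with V a velocity equal to flow Q divided by area πd²/4. Then V² is proportional to Q²/d⁴, and

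gradient ∝ Q1²/d1⁴ − Q2²/d2⁴.

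At a given flow, a wider anastomotic end lowers the gradient and a wider distal end raises it. For absolute pressure (mean arterial pressure minus gradient) both signs reverse. If flow itself rises with diameter, the dependence weakens. If each site's flow scales with its own d², then V no longer depends on d and the dependence disappears.

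Simulated cohorts of 90 show the range. Assumptions: median diameters 4.0 and 4.5 mm with log-SD 0.15 to 0.25, median flow 600 mL/min with log-SD 0.4, and mean arterial pressure SD 13 mmHg. None of these comes from the protocol. The table shows how often anastomotic-end diameter is significant against the gradient.

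| Flow scaling | Significant at .05 |
|---|---|
| Unrelated or proportional to diameter | 92–100% |
| Each site's flow proportional to its own d² | about 5% |

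Against absolute pressure the same test is significant in about 5% to 80% of cohorts, because variation in mean arterial pressure dilutes the coupling. That range takes V as mean velocity. If the velocity entered were a peak of twice the mean, the gradient would be four times as large (2² = 4) and the dilution weaker.

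A second set of assumptions used diameters of 4 and 5 mm with correlation 0.3, flow of 700 mL/min, and flow scaling with the diameter to the power b. The mean correlation of anastomotic diameter with the gradient was about −0.6 to −0.7 at b = 0, −0.2 to −0.3 at b = 2, and −0.1 to +0.1 at b = 3. I give no rate for the distal end, because it changes too much with the assumed correlation between the two diameters.

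**5. What a direct analysis could detect.** Take diameter compared by maturation status in 90 patients at a standardised difference of 0.6, borrowed from section 2.6. The noncentrality is 0.6·√(n1·n2/90), with 88 degrees of freedom. The 50% to 80% range for functional maturation comes from the Introduction.

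| Maturation | Split | Noncentrality | Power |
|---|---|---|---|
| 50% | 45/45 | 0.6·√22.5 = 2.85 | 0.80 |
| 70% | 63/27 | 0.6·√18.9 = 2.61 | 0.73 |
| 80% | 72/18 | 0.6·√14.4 = 2.28 | 0.61 |

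**The case against.** The strongest reply is that Aim 2 is titled and framed as a haemodynamic description, that its evidence is called preliminary, and that it is the first step of a programme whose second step is Aim 3. Its branch example is partly a diameter-pressure question, which Aim 2 can answer. All of this is fair, and the haemodynamic part of Aim 2 should stay. But calling evidence preliminary does not make it evidence about a different variable, and step 3 shows that the two-step chain fails on the protocol's own hypothesis.

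A second reply is that diameter may be among the unnamed predictors of the logistic regression. That is possible, so it cannot be said that diameter will never be tested against maturation, and unnamed predictors are not the fault here. Such a model would still not make the Aim 2 result support the sentence attached to it.

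A reader might go further and infer that the association is built into the formula, so that Aim 2 comes out positive almost whatever the truth and cannot return a negative answer. The document does not support that. The equation is not shown, and the terms described are V1, V2 and mean arterial pressure, with no diameter term. V is measured by Doppler rather than computed from the measured diameter, so the coupling is vessel physics, and its strength is an empirical matter. In step 4 significance ranges from about 5% to 100% with the assumptions, and the sign differs by segment.

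**Conclusion.** The point holds in limited form. The closing sentence of Aim 2 does not follow from the Aim 2 analysis, and Aim 3 does not repair it. That rests on the protocol's text alone. That the diameter-pressure association is partly mechanical is sound in direction but not in size: the figures rest on an assumed equation and on assumed diameters, flows and pressure variation. The fault is in the interpretation of one aim that the authors call preliminary. It leaves the primary outcome, Aim 3 and the 90 patients untouched. I rate it minor to moderate.

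**What to change.** Limit the Aim 2 conclusion to haemodynamics and delete the sentence on the role of diameter in maturation. Describe the diameter-pressure association as partly mechanical, because velocity depends on flow and cross-sectional area, and report it by segment and separately for gradient and absolute pressure.

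If a statement on diameter and maturation is wanted, add a logistic regression of spontaneous maturation on main-vein and branch diameter from the week-1 scan. The diameters, the outcome and the method are already in the protocol, so the cost is wording and one two-term model.

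The downside is modest power. The 0.80 to 0.61 above is for a two-group t test on one diameter, and a model with two correlated diameters may do worse. The 50% to 80% range also describes functional maturation generally, so the rate of unassisted maturation within 2 months may differ. The result should be reported as an estimate with its confidence interval, and a non-significant result should not be read as absence of a role.

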**Aim 3: To investigate the association between AVF luminal pressure and AVF maturation rate**

The pressure gradient and absolute luminal pressure in AVF will be calculated using the blood flow rates in different sites of the AVF. With these results, the association between pressure values and AVF maturation rates will be analyzed. These results may improve our understanding about the role of AVF luminal pressure at maturation. Moreover, valuable and modifiable risk factors for AVF maturation failure may be disclosed, which may be manipulable surgically or pharmaceutically in future.

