### Outcomes

2.5

The primary outcome of this study is spontaneous AVF maturation, which is defined as provision of sufficient blood flow for hemodialysis within 2 months of its creation without any interventional procedures. The secondary outcome is assisted AVF mature, which is defined as AVF maturation within 2 months from its creation, which is aided by any interventional procedure before successful use of AVF. The maturation time is defined as the period from the date of AVF creation to the date of the first successful employment for hemodialysis.

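### Calculated luminal pressure and the maturation outcome both derive from flow in the same fistula, so an Aim 3 association can arise from early flow alone, with size and sign left open

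*Protocol article*

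**What the plan says.** The exposure is a calculation. Section 2.4.2 (Laboratory analysis) states: "The AVF luminal pressure will be calculated from blood flow rates using the modified Bernoulli equation as described in the following section". Aim 3 in section 2.1.1 applies this to both versions of the exposure: "The pressure gradient and absolute luminal pressure in AVF will be calculated using the blood flow rates in different sites of the AVF". Aim 1 defines the absolute version: "We will also estimate the absolute AVF luminal pressure using the difference between the mean arterial pressure and AVF pressure gradient". Section 2.4.3 takes MAP from the other arm and defines the terms of the gradient: "V_1_ refers to the proximal blood flow rate, and V_2_ refers to the distal blood flow rate".

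Section 2.4.3 also uses the gradient itself as the pressure: "The luminal pressure in the radiocephalic AVF will be estimated by the pressure gradient from these two points". It does the same for the two brachial fistula types.

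The scan is early: "vascular sonography of the ipsilateral arm will be repeated within 1 week to measure the diameters, blood flow rates, and blood flow volume". Flow volume is thus available from the examination that supplies the pressure.

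Section 2.5 makes spontaneous maturation the primary outcome, "defined as provision of sufficient blood flow for hemodialysis within 2 months of its creation without any interventional procedures".

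Section 2.6 plans t tests and a multivariable logistic regression whose predictors are not named. The Abstract hypothesises that higher pressure is harmful. The Introduction hypothesises an optimal range, with some elevation needed and an excess harmful. Section 2.1 and the Discussion present pressure as something that surgery or drugs might change.

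**The concern.** MAP comes from the other arm, so the only information from the fistula in either version of luminal pressure is week-1 Doppler flow. The outcome is whether the same fistula later carries enough flow. If early flow predicts later flow, anything computed from early flow can be associated with maturation even when pressure plays no part. The analyses that are stated do not separate the two explanations.

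What is at stake is the reading of the main aim. A significant Aim 3 result could be presented as a role for pressure, and as a candidate target for treatment, when it may only restate week-1 flow.

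**Working it through.** **1. The plan's own figure.** A two-sample t test with d = 0.6, two-sided alpha 0.05, power 0.80 and ratio 1 gives 44.6, so 45 per group and 90 in all (power 0.804). The stated 90 is reproduced. The point concerns what the test can show, not the sample size.

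**2. Assumed form.** The displayed equations are not in the text available here. Assumed: gradient = 4(V1² − V2²), with m/s giving mmHg; absolute pressure = MAP − gradient; and the plan's flow rate read as a velocity. The documents give no velocities, areas or MAP values, so every input below is also an assumption.

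**3. Worked example, MAP 100 mmHg.**
- V1 = 2.0, V2 = 1.0: gradient 4(4 − 1) = 12, absolute pressure 88.
- V1 = 0.6, V2 = 0.3: gradient 4(0.36 − 0.09) = 1.08, absolute pressure 98.92.

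The slower fistula has the higher absolute pressure but the lower gradient. The two usages in the protocol rank these patients in opposite order.

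**4. When low flow means low velocity.** Velocity is flow divided by area, V = Q/A. With log-normal Q and A correlated at r on the log scale, cov(log V, log Q) = σQ(σQ − rσA), where σ² = ln(1 + CV²). Low flow goes with low velocity only while rσA < σQ.
- Flow CV 30% (σ = 0.294), area CV 40% (σ = 0.385): the sign turns at r = 0.294/0.385 = 0.76.
- Flow CV 50% (σ = 0.472), area CV 40%: 0.472 exceeds 0.385, so no r up to 1 turns it.

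The direction therefore depends on how anastomotic area and flow vary together, which the documents do not give.

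**5. Simulation with area unrelated to flow.** N = 90, maturation 50-80% (the range in the Introduction), median flow 500 mL/min, median areas 5 and 16 mm², flow CV 30-50%, area CV 20-40%, MAP 95 (SD 12) mmHg. Maturation depends on log flow only. Share of studies significant at 0.05:

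| Odds ratio per SD of log flow | Absolute pressure | Gradient | Either, after adding log flow |
|---|---|---|---|
| 2 | 20-47% | 31-65% | about 5-8% |
| 3 | 38-76% | 54-92% | about 5-8% |

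The absolute-pressure results run in the Abstract's direction. The gradient results run the other way if the gradient is called the pressure.

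**6. Same model, anastomotic area correlated with flow.** Maturation 65%, odds ratio 2, flow CV 30%, area CV 40%, 400 studies per setting. Nominal rate 2.5% in each direction.

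| Area-flow correlation | High absolute pressure with failure | Opposite direction |
|---|---|---|
| 0 | 23% | not reported |
| 0.5 | 5.5% | not reported |
| 0.8 | 1.8% | 6% |
| 0.8, with MAP-flow correlation 0.3 | 0% | 18% |

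With flow CV 50% and correlation 0.5, the rate in the Abstract's direction is 15%. The turn between 0.5 and 0.8 in the table agrees with step 4. A further run of this model with area correlated with flow found that adding log flow still held the error at about 3-8%.

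**7. A second model.** Here a latent flow quality drives both week-1 velocity and maturation, with V1 about 2 m/s, V2 about 1 m/s and MAP 100 mmHg.
- No carry-over from early flow to maturation: 2-4% of studies in the Abstract's direction.
- With carry-over: 9-94%, with a spurious d of 0.16 to 0.73 against the design effect of 0.6.
- MAP correlated with flow at 0.3: 2-54%, d −0.05 to 0.44.
- Poor flow appearing as a fast jet: sign reversed, d −0.23 to −0.78.
- Gradient read as the pressure: sign reversed, d −0.28 to −1.20.

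**The case against.** A reader might infer that the design must produce the hypothesised result because a poorly flowing fistula always scores a high pressure. The documents do not support that. The gradient depends on velocity, and a narrow anastomosis can combine low flow with a fast jet. Section 2.4.3 also uses the gradient as the pressure, which reverses the ranking. MAP can dilute or offset the artefact. The optimal-range hypothesis in the Introduction is not reproduced by an artefact that rises or falls steadily with flow. These objections stand, and they leave both sign and size open.

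It can also be said that flow volume is collected, that section 2.6 leaves its predictors unnamed, and that a covariate list may sit in a fuller document. That is fair, and the point does not rest on a missing list. It rests on what is stated: how the exposure is built, how the outcome is defined, and the use foreseen for the result.

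Finally, true pressure may act on early remodelling and so on week-1 flow. Adjusting for flow could then remove part of a real effect. At N = 90, sized for an unadjusted comparison, a non-significant joint test would settle little. This stands against making that test a condition for any claim. It does not stand against reporting the models side by side.

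**Conclusion.** The concern holds in a limited form. Because calculated pressure is a function of week-1 flow and the outcome is later flow, Aim 3 can show an association with no pressure effect. If absolute pressure is MAP minus gradient, and if low flow means low velocity, the artefact mimics the Abstract's hypothesis. With a narrow anastomosis, with MAP driving flow, or with the gradient read as the pressure, it shrinks or reverses.

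The simulated rates run from near zero to over 90% according to the assumptions. They show that the problem can be large, not how large it is in this study. They rest on the assumed equation and on assumed velocities, areas, MAP and correlations. The good behaviour after adding log flow also assumes that flow volume is recorded without error; with noisy flow, some of the artefact would remain. This is a worthwhile, cheap improvement and not a condition for proceeding.

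**What to change.** In section 2.6, for Aim 3, report three logistic models of spontaneous maturation: (a) week-1 log flow volume, (b) calculated pressure, (c) both. Do this separately for the gradient and for absolute pressure. Add a sensitivity model in which MAP has its own term beside the gradient and log flow volume; MAP, gradient and absolute pressure cannot all enter together, because the third is the difference of the first two. Reserve the term luminal pressure for one definition and use it throughout sections 2.1.1 and 2.4.3.

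State in advance that a pressure association that does not persist alongside flow volume will be reported as not distinguishable from early flow, and not as evidence for pressure as a modifiable target. Judge persistence from the estimate and interval in (c), without using the likelihood-ratio test as a pass/fail gate.

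No new data are needed. The cost is precision: under the assumptions of step 5, variance inflation is about 1.1-1.5 for absolute pressure and 1.4-4.8 for the gradient. Intervals on the log-odds scale widen by the square root, about 1.05-1.22 and 1.18-2.19 times. Model (c) may also over-adjust if early flow carries part of a true pressure effect, which is why (b) should be shown beside it.
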